# II. Introduction and problem statement

Dengue is a viral vector-borne disease, predominantly affecting the urban areas but extending into more populated rural areas. The main insect vector is the highly synanthropic *Aedes aegypti* mosquito. The vector breeds in water storage containers and other deposits containing relative clean water, and bites and rests in and around human dwellings. Attempts at eradication failed during the 1960s in Latin America and today more than 50% of houses are infested with *Aedes* larvae in many endemic areas (WHO HQ 2000;PAHO 1994).

Dengue prevention has long depended on control of immature vector populations either by insecticidal treatment (larviciding) or removal of breeding sites and occasionally, biological control. These interventions showed a variable success and are in most of the countries difficult to sustain.

Control of immature stages impacts only on vector densities and not on mosquito longevity or other key parameters affecting dengue transmission: targeting adult vectors is more likely to reduce both transmission and mosquito density. The WHO Dengue Scientific Working Group of 2006 identified the development and evaluation of Insecticide-treated materials (ITM) as a primary global research stream. ITM, highly effective in preventing malaria and other nocturnally transmitted vector-borne diseases, have shown a first proof of efficacy on dengue vector densities and potentially on dengue transmission in Venezuela and Mexico (Kroeger et al. 2006). In a recent study in Thailand and Venezuela, it was observed that the use of the ITM curtains declined rapidly over time (Vanlerberghe et al. 2011a) and its effect was shown to be coverage dependent (Vanlerberghe et al. 2011b). The purchase price of the curtains is high, which result in a high strategy cost when implemented by the routine control programme: 1.9 USD per curtain distributed (of which 77% for the curtain itself) (Baly et al. 2011).

Besides being a partial barrier for mosquito entry in houses, the insecticide treated curtains essentially deliver a residual insecticide targeting adult mosquitoes inside the house and may prove an effective alternative to Indoor Residual spraying in targeting adult dengue vectors (Esu et al. 2010).

Perifocal indoor residual spraying has been repeatedly used in Cuba (however few reports of such intervention in other parts of the world are available), but its effect has not been systematically documented. Variable success was observed depending on the insecticide used. In this procedure, a residual formulation of an adulticide is sprayed with a compression sprayer (Hudson type) on the walls of watertanks and its surroundings together with potential *Aedes* resting sites inside the houses (sites where mosquitoes rest after/in between blood meals).

Space spraying with adulticides have been widely and often used in the past by the routine vector control programme of Cuba. From 1981 to 1986 malathion was used as an ultra low volume spray; from 1986 up to present pyrethroids (cypermethrin and Lambda-cyhalothrin) have been used in fogging campaigns during periods of high mosquito infestation levels or during dengue outbreaks (as in Santiago de Cuba in 1997 and 2006 and Havana City 2001-2002). Other products as Bendiocarb have also been occasionally used in the last years (2008 up to now).

Recently, the laboratory of IPK (Institute of Tropical Medicine ‘Pedro Kouri’) evaluated the susceptibility of the 2010 local *Aedes aegypti* strain of Santiago de Cuba. The local strain was found to be resistant to Lambdacyalothrin 0.05%, Bendiocarb 0.1% and DDT 4%. The strain was susceptible for deltamethrin 0.05% and Malathion 5%.

Following these observations, it was decided to compare the deltamethrin treated curtains with peri-focal spraying of deltamethrin (malathion being badly accepted by the population in the past) in Santiago, a municipality where the baseline *Aedes* infestation already reached low levels, but where transmission still occurs.

# III. Research objectives and hypothesis

## *III.A. General Objective*

Compare the acceptance, effectiveness and cost-effectiveness of Insecticide treated curtains (ITC) distribution and of peri-focal insecticide spraying (PFS) to control *Aedes* and dengue.

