## *III.B. Specific objectives*

1. Evaluate the uptake and acceptability of tools in both intervention arms (ITC and PFS)
2. Evaluate the effectiveness of both tools, on top of the routine, in the control of *Aedes aegypti* (in comparison to the effect of the routine programme alone)
3. Compare the cost-effectiveness of both tools with the routine *Aedes* control strategy

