# IV. Methodology

## *IV.A. Description of study* **and study areas**

The study is planned to take place in urban Santiago de Cuba. Santiago is one of the Cuban municipalities where *Aedes aegypti* foci are most frequently reported, despite continuous surveillance and vector control activities. In 1981 it was affected by an epidemic that spread across the country and in 1997, 2001, 2002, 2006 and 2008 by epidemic outbreaks that remained rather limited. Santiago de Cuba is located in the Eastern part of the island, in the province of the same name. The average temperature oscillates between 30 and 32 °C and rainfall is scarce. The municipality is the most densely populated one of the whole country and has 475 580 inhabitants, of which eighty-seven percent live in the urban zone. There are residential settlements under construction and the periurban neighbourhoods lack adequate sanitary conditions. Water is supplied, on average, every 3 days, but since there were in the last decades major damages to the piped water system, the population is used to store drinking water at home in multiple containers. Garbage collection is sometimes deficient, which leads to accumulation of trash.

Design:

Cluster-randomized controlled trial with 2 years follow up of interventions. Intervention and control clusters will be selected out of all urban municipalities (except Fran Pais and Julian Grimau).

Cluster = a house block with its 4 surrounding house blocks; containing approx. a total of 250 houses

Clusters with the highest infestation – levels (entomological information from January to December 2009) will be selected. The selection procedure will assure that there are no common boundaries between clusters, as a certain spill-over effect can be expected (Kroeger et al. 2006). Afterwards, clusters will be randomly allocated to the control, ITC or PFS intervention arm.

Sample size estimation (based on the effectiveness of curtains, measured through entomological indices):

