The Breteau index (BI) was on average 2 per 100 houses in 2009. With the interventions, we aim to decrease the BI with 50% to 1/100 houses. Based on the Hayes and Bennett sample size estimation (Hayes & Bennett 1999), using an inter-cluster variation coefficient of 0.5, we need a minimum of 20 clusters of 250 houses in each arm to demonstrate the effect of the ITC or PFS intervention in comparison to the control arm. We increased the number of clusters with 5% and hence will have a final sample size of 21 clusters of 250 houses/study arm. Totaling 63 clusters of on average 250 houses for the entire study.

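### The general objective compares ITC with PFS, but only tool-versus-control is sized and arms are compared survey by survey; a single whole-follow-up estimate is needed for the head-to-head

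*Protocol*

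**What the plan says.** Two places in the protocol set the tools against each other. The introduction (section II) concludes that "it was decided to compare the deltamethrin treated curtains with peri-focal spraying of deltamethrin". Section III.A gives as the general objective: "Compare the acceptance, effectiveness and cost-effectiveness of Insecticide treated curtains (ITC) distribution" and the same for PFS.

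The specific objectives are narrower. In III.B, objective 2 judges both tools, added to routine control, "in comparison to the effect of the routine programme alone", and objective 3 does the same for cost-effectiveness.

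The sizing in IV.A follows the specific objectives. It starts from "The Breteau index (BI) was on average 2 per 100 houses in 2009" and states that "we aim to decrease the BI with 50% to 1/100 houses". With a between-cluster coefficient of variation of 0.5 it arrives at 20 clusters of 250 houses per arm "to demonstrate the effect of the ITC or PFS intervention in comparison to the control arm", raised by 5% to 21. Both tools are given the same target, so the planning difference between them is zero. No ITC versus PFS difference, margin or power is given.

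Section IV.C states the effectiveness analysis: infestation is compared between the intervention arms at each time point, allowing for pre-intervention levels and clustering, with negative binomial random-effects models. Larval surveys take place at least monthly for two years.

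**The concern.** A reader who takes the general objective at its word will look for the answer to curtains or spraying. The one contrast that answers it directly was not sized, and the stated method spreads it over about 24 monthly comparisons, each resting on one survey. At a Breteau index of 1 per 100, a cluster of 250 houses yields about 2.5 positive containers per survey, so each monthly contrast is imprecise.

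At stake is how informative the head-to-head result can be. A run of inconclusive monthly comparisons says little about which tool leaves less infestation, while the same data summarised once would say more.

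**Working it through.** **Inputs.** From IV.A: Breteau index 0.02 per house under control and 0.01 under either tool, y = 250 houses per cluster, k = 0.5, 21 clusters per arm. From IV.C: at least monthly larval surveys over 2 years, so about 24 rounds. Assumed, because the protocol does not state them: two-sided 0.05 and 80% power.

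**Formula (Hayes-Bennett, unmatched).** c = 1 + (1.96 + 0.84)² × V / (λ0 − λ1)², with V = (λ0 + λ1)/y + k²(λ0² + λ1²). For power at given c: Φ{√[(c − 1)(λ0 − λ1)²/V] − 1.96}.

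**Step 1: reproduce the plan.** V = 0.03/250 + 0.25 × (0.0004 + 0.0001) = 0.000120 + 0.000125 = 0.000245. Then c = 1 + 7.85 × 0.000245/0.0001 = 20.2, which matches the stated 20. At 21 clusters, power against control is 81.5%. Of the standard settings tried, this pair of error rates is the one that returns about 20 (90% power two-sided gives 26.7; 80% one-sided gives 16.2).

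**Step 2: ITC versus PFS, one survey, one tool at 0.01.**
- Other tool at 0.0075 (25% lower): V = 0.0175/250 + 0.25 × 0.00015625 = 0.0001091. √(20 × 0.0025²/0.0001091) = 1.07; Φ(1.07 − 1.96) = 19%.
- Other tool at 0.005 (further halving): V = 0.015/250 + 0.25 × 0.000125 = 0.00009125. √(20 × 0.005²/0.00009125) = 2.34; Φ(2.34 − 1.96) = 65%.
- Solved for 80% power, the other tool would have to be at about 0.42 per 100, or 58% lower.

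**Step 3: precision if the tools are equal, one survey.** Expected positive containers per cluster E = 250 × 0.01 = 2.5. SE of the log ratio = √[2(1/2.5 + 0.25)/21] = 0.249. 95% CI factor = exp(1.96 × 0.249) = 1.63, so about 0.61 to 1.63.

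**Step 4: whole follow-up.** Pool 24 rounds as independent within cluster, which is optimistic: y = 24 × 250 = 6000 and E = 60.
- 25% difference: V = 0.0175/6000 + 0.25 × 0.00015625 = 0.00004198; √(20 × 0.0025²/0.00004198) = 1.73; power 41%.
- Further halving: V = 0.015/6000 + 0.25 × 0.000125 = 0.00003375; √(20 × 0.005²/0.00003375) = 3.85; power 97%.
- 80% power at about 0.62 per 100, or 38% lower.
- Equal tools: SE = √[2(1/60 + 0.25)/21] = 0.159; CI about 0.73 to 1.37.

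**Step 5: baseline adjustment.** IV.C plans it, and it could act like a smaller k. The protocol gives no adjusted k, so a range is shown for the 25% difference.

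| k (assumed after adjustment) | One survey | 24 surveys pooled |
|---|---|---|
| 0.5 (no gain) | 19% | 41% |
| 0.4 | 21% | 56% |
| 0.35 | 22% | 66% |
| 0.3 | 23% | 77% |
| 0.25 | 24% | 88% |

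In a single survey, adjustment barely helps, because the small count dominates V. Over the whole follow-up it helps considerably.

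**The case against.** The strongest reply is that the confirmatory question is already settled. Specific objectives 2 and 3 judge both tools against routine control, and the sizing matches them. A broad general objective made operational by narrower ones is not a contradiction. This largely stands: the sample size is not wrong, and the change to III.A is an alignment of wording.

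A reader might infer that the protocol will treat a non-significant ITC versus PFS result as proof that the tools work equally well. The text does not support that. It states no equivalence or non-inferiority claim, and IV.C names no test, p-value or significance level. The phrase about comparing intervention arms is itself ambiguous: IV.A uses similar wording for all three arms, III.B for ITC and PFS only.

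A reader might also infer that imprecision in the head-to-head goes unnoticed into the cost-effectiveness result. It does not. The cost-effectiveness text in IV.C already plans 95% confidence intervals for cost and indices across the three arms, and a percentile bootstrap with 1000 estimates for the incremental ratio. No step there depends on whether ITC and PFS differ significantly.

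Finally, details of estimation may sit in an analysis plan that is not shown. That is fair for matters the protocol leaves open, but the protocol itself states the per-time-point comparison. That stated choice is what gives the head-to-head its weakest form.

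**Conclusion.** The point holds as a modest, low-cost improvement. The head-to-head named in the objective and rationale is unsized, and survey-by-survey comparison gives it 19% to 24% power for a 25% difference across k from 0.5 down to 0.25. One estimate over the whole follow-up raises this to 41% at the protocol's own k, and to about 66% if adjustment lowers k to 0.35. It also narrows the interval for equal tools, at k = 0.5, from 0.61–1.63 to 0.73–1.37.

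It would be too strong to say that the trial cannot detect a moderate difference between the tools under any analysis. With pooled surveys, a further halving is detectable with 97% power even at k = 0.5, and a strong baseline correlation could make a 25% difference detectable too.

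The figures rest on two-sided 0.05, on one tool reaching the planned index of 1 per 100, and, when pooled, on independence of rounds within cluster. The adjusted values of k are assumptions.

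**What to change.** 1. In III.A, say that each tool versus routine control is the confirmatory effectiveness question, in line with specific objectives 2 and 3, and that ITC versus PFS is an estimated contrast.
2. In IV.C, pre-specify ITC versus PFS as one baseline-adjusted rate ratio with 95% CI over the whole follow-up, from the planned negative binomial random-effects model. State the detectable difference beside it: about 38% under the pooled assumptions above with k = 0.5, to be revised if a baseline-adjusted k can be justified.
3. Keep the comparisons at each time point as descriptive.

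Leave the cost-effectiveness section as it is.

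This needs no extra clusters, surveys or data. The price is a less ambitious head-to-head claim and less emphasis on effects at particular times.

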## *III.B. Specific objectives*

1. Evaluate the uptake and acceptability of tools in both intervention arms (ITC and PFS)
2. Evaluate the effectiveness of both tools, on top of the routine, in the control of *Aedes aegypti* (in comparison to the effect of the routine programme alone)
3. Compare the cost-effectiveness of both tools with the routine *Aedes* control strategy

# IV. Methodology

## *IV.A. Description of study* **and study areas**

The study is planned to take place in urban Santiago de Cuba. Santiago is one of the Cuban municipalities where *Aedes aegypti* foci are most frequently reported, despite continuous surveillance and vector control activities. In 1981 it was affected by an epidemic that spread across the country and in 1997, 2001, 2002, 2006 and 2008 by epidemic outbreaks that remained rather limited. Santiago de Cuba is located in the Eastern part of the island, in the province of the same name. The average temperature oscillates between 30 and 32 °C and rainfall is scarce. The municipality is the most densely populated one of the whole country and has 475 580 inhabitants, of which eighty-seven percent live in the urban zone. There are residential settlements under construction and the periurban neighbourhoods lack adequate sanitary conditions. Water is supplied, on average, every 3 days, but since there were in the last decades major damages to the piped water system, the population is used to store drinking water at home in multiple containers. Garbage collection is sometimes deficient, which leads to accumulation of trash.

Design:

Cluster-randomized controlled trial with 2 years follow up of interventions. Intervention and control clusters will be selected out of all urban municipalities (except Fran Pais and Julian Grimau).

Cluster = a house block with its 4 surrounding house blocks; containing approx. a total of 250 houses

Clusters with the highest infestation – levels (entomological information from January to December 2009) will be selected. The selection procedure will assure that there are no common boundaries between clusters, as a certain spill-over effect can be expected (Kroeger et al. 2006). Afterwards, clusters will be randomly allocated to the control, ITC or PFS intervention arm.

Sample size estimation (based on the effectiveness of curtains, measured through entomological indices):

The Breteau index (BI) was on average 2 per 100 houses in 2009. With the interventions, we aim to decrease the BI with 50% to 1/100 houses. Based on the Hayes and Bennett sample size estimation (Hayes & Bennett 1999), using an inter-cluster variation coefficient of 0.5, we need a minimum of 20 clusters of 250 houses in each arm to demonstrate the effect of the ITC or PFS intervention in comparison to the control arm. We increased the number of clusters with 5% and hence will have a final sample size of 21 clusters of 250 houses/study arm. Totaling 63 clusters of on average 250 houses for the entire study.

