K-Othrine 25 WG, supplied by Bayer Environmental Sciences co. (25% deltamethrin formulation) will be sprayed every 4 months (3 times/year). It is a granular formulation that need to be solved into water (20 gram in 8 Liter of water, sufficient to treat 200 m² and attaining 25 mg a.i./m²). It has a long lasting residual activity. Where deposits remain undisturbed, residual activity depends upon the nature of the surface (Rojas de Arias et al. 2004;Rozilawati et al. 2005). Sustained residual activity beyond 12 weeks post-application is observed on non-porous surfaces. Deltamethrin is photostable and the particulate suspension enhances availability to insects.

The insecticide will be sprayed on the outside of the ground-level water tanks and the walls behind them; and on the adult *Aedes* resting sites (for example under beds, in and under closets) in the intradomestic area.

Teams of health workers of the routine *Aedes* control programme will be trained to realize this activity and standard operating procedures are designed. A short movie has been made to show the correct application of insecticide to all implementers. Control visits by supervisors will be done on a regular basis during application to assure quality of action.

The PFS will be done in the houses, but also public places, as working areas, schools, cultural centra will be included as far as possible.

Before distribution the consent of the users will be procured in a community meeting and a written informed consent will be obtained on the moment of spraying. Information on the product and its possible side effects will be provided to the communities in the preparative community meetings and to each household before spraying starts.

The procedure of implementation is detailed in annex 4.

The set-up of the ITC and PFS interventions will be done by a local research group and by the routine vector control programme. The former will be responsible for its implementation, coordination with the local health authorities, documentation of process and organization of training sessions according to the needs of the actors involved.

Routine *Aedes* Control activities

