## *IV. C. Data collection and analysis*

Effect measures:

Primary outcomes:

Effectiveness: Breteau Index, House index, Pupae per person index, (adult mosquito infestation)

confirmed Dengue cases (if any). Comparison of infestation at each time point between the intervention arms, taking into account the pre-intervention infestation levels and the cluster design. Generalized linear random effect regression models with a negative binomial link function will be used.

Secondary output:

Uptake and use of ITC

Acceptance of PFS and ITC (and identification of underlying lay dimensions of acceptability)

Change in intra-and extradomiciliary risks for Aedes infestation

Cost- effectiveness of ITC and of PFS

Residual insecticidal activity of deltamethrin applied in ITC and in PFS

Data collection:

1. Baseline study (in both intervention and control arms) :
   1. Entomological survey:

Existing of larval and pupal surveys; the larval surveys will be conducted as in the routine system (exhaustive inspection of all houses and potential water holding containers on the presence of immature stages of Aedes). The traditional Stegomyia indices will be calculated: the House Index (HI) and Breteau index (BI). Collection of adult mosquitoes: during routine surveys, the vector control teams are also inspecting houses in the search of adult mosquitoes.

The pupal surveys will consist of direct inspection of potential water-holding containers inside and around the houses following the recommendations of Focks (Focks 2004). This will be done by a special team in 20% of the house-blocks (randomly chosen: 23 houseblocks/arm). All containers where immature stages of Aedes are detected will be emptied and the absolute number of pupae will be counted. For elevated water tanks a sweeping method will be used to collect the majority of the pupae. The total number of positive containers for Ae. aegypti pupae and their relative contribution to total pupal production will be recorded and computed. The number of persons per house will be also enquired (during the distribution of tools) for the construction of Pupal Index per inhabitant (PPI) at the cluster level.

- 1. Evaluation of main intra and extra domiciliary risks at household and environmental risks at community level in each houseblock included in the study: data collected by the routine vector control programme teams through observation, guided by an observation guide (Annex 5).

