     1. ITC (monitoring insecticide content of PermaNet curtains over time): These bioassays will be done using two methods of exposure: cone method and tube method. In both, the same procedure will be followed: 10 cones/tubes per curtain, 5 female *Aedes* mosquitoes per cone/tube, 3-5 days old, non-blood fed, exposure of 3 minutes, evaluation of knock down after 3’ and 1 hr and mortality after 24 hr. This will be done at 4 time moments (or shorter if decline of residual effect): on a sample of 2 curtains before distribution (non-used ITC to evaluate batch quality), on a sub-sample of 10 curtains, after 6, 12, 18 and 24 months of use. In the 6 month assay, ITC will be collected in 10 houses of vector control workers (where washing procedures and washing frequency and other characteristics of use will be recorded in a prospective way). In the surveys of 12 and 24 months, a random sampling will be done. Additionally a subsample of the curtains (one ITC which gives mortality below 80%, one with mortality between 80-95% and one with mortality > 95%) will be evaluated through HPLC to define the residual deltamethrin concentration (Laboratorio de registro de plaguicidas en Cuba, a certified center in Havana).
     2. PFS:
        - Bio-assays (cone method, with 15 female *Aedes* mosquitoes/cone; 3-5 days old, non-blood fed, exposure of 1 hour – transference to clean cups, observation of knock down/mortality after 1 hour and after 24 hours)
        - Selection of houses: 4 houses (one per health district) with previous indication of surfaces to be tested; and 4 houses (randomly chosen, one per district) with no previous indication of surfaces to be tested
        - Test of : 2 cones on metal surface; 2 cones on wooden surface, 2 cones on cement surface and 2 cones as control on a non-sprayed surface.
        - Frequency: 1 day, 1 week, 2 weeks, 3 weeks, 4 weeks, 2 months, 3 months and 4 months after spraying (or stopped earlier if no mosquito mortality is observed). This will be done after the first application and will be repeated in the second year of application.
  3. Resistance testing of the local Aedes aegypti strains to deltamethrin and other insectcides (as done in baseline) using the WHO standardised impregnated papers (see annex 6 for methodology). Evaluation with one year intervals (starting from baseline): mid 2011, mid 2012 and in 2013 when study finished.

1. Cost-effectiveness evaluation

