**Critical assessment and possible limitation of the study design and methodology in relation to project objectives:**

The main limitation is the use of the routine entomological information to compare the effectiveness between study groups: this data collection has standardized procedures. However different vector control technicians are collecting it and few data can be (randomly) missing. We will improve the quality assurance system in place to secure validity of the measurement of entomological variables.

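### Allocation is not restricted on cluster data already held, which costs some precision; separately, the programme that sprays also records the Breteau and House indices with no separation of the two roles

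*Protocol*

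**What the plan says.** **Allocation.** Protocol section IV.A: "Clusters with the highest infestation – levels (entomological information from January to December 2009) will be selected". After a condition that clusters share no boundary, it continues: "Afterwards, clusters will be randomly allocated to the control, ITC or PFS intervention arm". No method of randomisation and no balancing factor is given there or elsewhere. Section IV.A sizes the trial at 21 clusters of 250 houses in each of three arms (63 in all), from a mean BI of 2 per 100 houses, a 50% reduction and a between-cluster coefficient of variation of 0.5.

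**Geography.** Sections IV.B and IV.D speak of health areas. The only count of districts is implied by the spray bioassays in section IV.C: "4 houses (one per health district) with previous indication of surfaces to be tested".

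**Who treats and who measures.** Section IV.B, on peri-focal spraying (PFS): "Teams of health workers of the routine *Aedes* control programme will be trained to realize this activity". It also gives the routine programme, with a local research group, a part in setting up both tools. For the outcomes, section IV.C says that "the larval surveys will be conducted as in the routine system", at baseline and follow-up, and adult mosquitoes are sought during the same routine surveys. Pupae are counted by a dedicated team in 20% of house-blocks.

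**Analysis and safeguards.** The model in section IV.C adjusts for pre-intervention infestation and for clustering; it names no district or team term. The critical assessment calls reliance on routine entomological data the main limitation: "However different vector control technicians are collecting it and few data can be (randomly) missing". It promises better quality assurance. Section IV.D says that routine quality control covers 60% of households.

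**The concern.** Two separate matters are involved.

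1. **Precision.** Each cluster's 2009 infestation is in hand before allocation, and its location is known. Leaving both out of the allocation accepts chance imbalance that could be avoided at almost no cost, in a trial whose size has little reserve. Balance has to be built in at allocation.

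2. **Detection.** BI, the index on which the trial is sized, comes from a programme that knows where it has sprayed. If recording becomes less complete in treated clusters after the intervention starts, the BI ratio moves in the tool's favour. Baseline adjustment cannot correct a change that begins after baseline. At a BI of 2 per 100, a cluster of 250 houses yields about 250 × 0.02 = 5 positive containers per survey, so one missed container is 20% of the count.

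**Working it through.** **Step 1. Reproduce the sample size.** Inputs from section IV.A: λ0 = 0.02, λ1 = 0.01, y = 250 houses, k = 0.5. Alpha and power are not stated; two-sided 0.05 and 80% are assumed. Unmatched Hayes-Bennett formula:

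c = 1 + (1.96 + 0.84)² × [(λ0 + λ1)/y + k²(λ0² + λ1²)] / (λ0 − λ1)²

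= 1 + 7.849 × [0.00012 + 0.000125] / 0.0001 = 20.23

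This agrees with the stated minimum of 20, and 20 × 1.05 = 21. The formula gives 81.5% power at 21 per arm, so the reserve is small. It uses no stratification.

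**Step 2. Chance baseline imbalance under simple allocation.** SD of the difference in true mean BI between two arms:

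√(2/21 × k² × λ0²) = √(0.0952 × 0.25 × 0.0004) = 0.0031, or 0.31 per 100 houses

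That is 0.31/2 = 15% of the mean, with a 95% range of about ±30%. If k were 0.3, it would be 9% of the mean. These figures are before any adjustment.

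**Step 3. What restriction would gain.** The simulation allocated 63 clusters 21/21/21 over four districts of 16, 16, 16 and 15 (assumed sizes) and compared one tool arm with control. Counts were Poisson with total CV 0.5. Districts carried 25% or 50% of between-cluster log-variance (assumed). There were 6,000 runs per cell; the Monte Carlo SE of a power near 85% is √(0.85 × 0.15/6000), about 0.5 points.

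| Allocation | District term | Type I error (25% / 50% share) | Power (25% / 50% share) |
|---|---|---|---|
| Simple | no | 4.5% / 4.5% | 84.7% / 84.4% |
| Simple | yes | 5.1% / 4.5% | 84.8% / 90.2% |
| By district | no | 3.5% / 2.6% | 86.2% / 85.9% |
| By district | yes | 5.0% / 4.8% | 88.6% / 92.4% |

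From the first row to the last, the gain is 88.6 − 84.7 = 3.9 and 92.4 − 84.4 = 8.0 points. The term matters as well as the allocation: stratifying without it makes the test conservative. Conversely, at the 50% share the term alone brings 90.2 − 84.4 = 5.8 of the 8.0 points. The simulation stratified on district only and fitted no baseline covariate, so it does not measure the gain over the planned baseline-adjusted model.

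**Step 4. Detection.** If inspectors record a fraction d of foci in treated clusters relative to control, the recorded ratio is the true ratio × d. The documents give no d. For assumed values of 0.9, 0.8 and 0.7, a tool with no effect would appear to reduce BI by 10%, 20% and 30%, against a target of 50%. Balancing districts leaves this unchanged, because every district would still contain treated clusters inspected by the workforce that treats.

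**The case against.** The case against is substantial.

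- **Silence is not exclusion.** The protocol does not rule out restricted allocation. That stands, but allocation is a matter for the protocol, and this text fixes no method.
- **Imbalance is already provided for.** The 0.31 SD follows from the k of 0.5 that the sample size includes, and the model adjusts for pre-intervention infestation. Both are true. They make the first point one of efficiency.
- **Detection is partly guarded.** Pupae have their own team, quality assurance is to be improved, and routine workers also carry out control work in the control arm. These reduce the concern. They do not separate roles for BI and House index. Annexes 3 and 4, which detail how the tools are implemented, are not at hand and may say more.

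Three stronger readings are tempting and are not supported:

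- A reader might infer that district teams both spray and record the outcome. The protocol speaks of routine programme teams; it does not say that they are organised by district, or that the same individuals do both jobs.
- A reader might infer that simple allocation loads team or baseline differences onto an arm as bias. It does not: the estimate is centred correctly, and simulated type I error was 4.5% with simple, unadjusted allocation.
- A reader might count clusters. With the assumed district sizes, about 62% of simple allocations leave some district with an arm gap of five or more. That is not an error in the BI ratio. Even if one district recorded only half of its foci, the spurious ratio would have a 95% range of 0.87 to 1.15, centred on 1.

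**Conclusion.** Both points hold, as moderate design weaknesses.

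**Precision:** avoidable chance imbalance with an unadjusted SD of about 0.31 BI points (15% of the mean), and roughly 4 to 8 power points forgone. The power figure rests on four near-equal districts carrying 25% to 50% of between-cluster variance, and on a comparison without baseline adjustment. The gain over the planned model could be smaller. Validity is not at stake.

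**Detection:** the programme that sprays also produces BI and House index, and no section of the protocol keeps the two tasks apart. The size of any resulting bias cannot be derived from the document; step 4 shows only how it would pass into the ratio. It is a separate issue from allocation and needs its own remedy.

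**What to change.** **Allocation, before clusters are assigned.** State the method and restrict it. For example, rank clusters by 2009 BI within district, form sets of three and randomise each set to the three arms; alternatively, use constrained randomisation that keeps 21/21/21. Add a district term to the model beside baseline infestation. The cost is slightly more allocation work, since district sizes may not divide by three. With four districts, up to two clusters may be left over in each, at most eight. Because 63 is a multiple of three, the leftovers total at most six and form no more than two mixed sets. If clusters are already allocated, only the district term can still be added.

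**Detection.** Arrange the inspection rota so that no worker inspects a cluster that the same worker sprayed or supplied with curtains. Tabulate by arm the discrepancies found in the existing 60% quality control, as a check on detection bias. The first is a small rota change. The second is cheap if discrepancies are recorded; the protocol does not say that they are, so recording them may have to be added.
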